## Abstract

**Background:**

Young people with first episode psychosis are at an increased risk for a range of poor health outcomes. In contrast to the growing body of evidence that suggests that exercise therapy may benefit the physical and mental health of people diagnosed with schizophrenia, there are no studies to date that have sought to extend the use of exercise therapy among patients with first episode psychosis. The aim of the study is to test the feasibility and acceptability of an exercise program that will be delivered via internet enabled mobile devices and social networking technologies among young people with first episode psychosis.

**Methods/Design:**

This study is a qualitative pilot study being conducted at Orygen Youth Health Research Centre in Melbourne, Australia. Participants are young people aged 15-24 who are receiving clinical care at a specialist first episode psychosis treatment centre. Participants will also comprise young people from the general population. The exercise intervention is a 9-week running program, designed to gradually build a person's level of fitness to be able to run 5 kilometres (3 miles) towards the end of the program. The program will be delivered via an internet enabled mobile device. Participants will be asked to post messages about their running experiences on the social networking website, and will also be asked to attend three face-to-face interviews.

**Discussion:**

This paper describes the development of a qualitative study to pilot a running program coupled with the use of internet enabled mobile devices among young people with first episode psychosis. If the program is found to be feasible and acceptable to patients, it is hoped that further rigorous evaluations will ultimately lead to the introduction of exercise therapy as part of an evidence-based, multidisciplinary approach in routine clinical care.

## Background

Young people experiencing their first episode psychosis are at an increased risk of poor health outcomes, such as weight gain [1], cardiovascular disease and diabetes [2,3], and often present with significant medical co-morbidities [4]. Poor dietary choices, infrequent physical activity, and side effects from antipsychotic medications are some of the factors that are thought to account for the elevated levels of physical morbidity among this population [5,6]. Others have gone further to suggest that it is the general health and mental health systems that have shown a lack of concern about the physical health of people with mental illness [7]. While physical exercise has surprisingly been a neglected intervention in mental health treatment packages [8], there has been a growing recognition that physical activity can aid in the process of psychiatric rehabilitation [9], with potential benefits for both physical and mental health [10].

The effectiveness of exercise as an adjunct therapy for established psychotic disorders was the subject of a recent critical review that showed good support for the improved mental health among participants following an exercise intervention [11]. While the quantitative findings were relatively weak, partly due to the small numbers of participants, findings from the qualitative interviews were more positive. Participants reported more positive psychological well-being and social interaction with family and friends following the intervention [12,13]. These findings are bolstered by randomised controlled trials that found significantly greater reductions in body fat [14] and significant improvements in depression, anxiety [10,15] and negative symptom scores [10,14] among experimental participants compared to controls. One trial compared yoga therapy with exercise therapy and found that while yoga therapy participants showed significantly reduced levels of psychopathology and greater quality of life when compared to physical exercise participants, both groups demonstrated an increase in social and occupational functioning [10,16].

No studies to date however, to the knowledge of the authors, have specifically investigated the physical and mental health benefits of exercise therapy among young people with first episode psychosis. Exercise Interventions in the early course of psychosis may lead to marked gains in health benefits for these young people [17]. Given the popularity of the internet among young people, the current study will pilot the use of internet enabled mobile devices to assist young people with mental illness to engage in a publicly available exercise program called *Couch to 5K *(C25K), which may assist in overcoming geographical barriers in attending regular onsite exercise classes [15]. The study will also utilise social network technologies to overcome motivational barriers in increasing and maintaining physical activity in everyday life [18]. Social interaction is important for an individual's wellbeing, and social networks provide the means to link individuals together to create a group dynamic and facilitate social interaction [19]. These social interactions between individuals and their influences on each other on the social network website may also facilitate behaviour change in relation to jogging, as the technology will allow other individuals to see when others are jogging, for how long and how far, encouraging others to exercise and be active also. This field of persuasive techniques is known as persuasive technology, which has been defined as technology that is intentionally designed to change a person's attitude or behaviour [20,21]. Persuasive technology can have a positive impact on the fitness of young people [22], and may assist in circumventing the poor health outcomes among patients with first episode psychosis.

The overall aim of this study is to develop a prototype and test services delivered through internet enabled mobile devices and social network technologies that are designed to encourage young people to engage in physical exercise as well as act as an intervention for weight gain. The study will also seek to investigate if the delivery of an exercise program via this medium would be acceptable to young people.

## Methods

### Study design

The study is a qualitative pilot study that is designed to explore the feasibility and acceptability of using internet enabled mobile devices and social network technologies in promoting exercise among young people. The study has been approved by Melbourne Health Human Research Ethics Committee.

### Setting

Orygen Youth Health (OYH) is a specialist public mental health service for people aged 15-24 years living in the Western and Northern regions of Melbourne. The service treats young people presenting with psychotic and non-psychotic disorders. The catchment area covers a population of approximately one million people. The study will take place in the Early Psychosis Prevention and Intervention Centre (EPPIC), a clinical program at Orygen Youth Health. EPPIC was established in 1992 with the aim of reducing the delay in detecting and treating psychosis and advocates for timely and comprehensive treatment during the early years following illness onset [23]. All people aged between 15 and 24 who are living in the catchment area and experiencing a first episode of psychosis are referred to this service and may receive clinical care for a period of 18 months.

### Participants

Inclusion criteria for the study include: (1) being a current client at EPPIC; and, (2) express an interest in participating in a running program, to ensure that they will complete the program and are willing to volunteer their time. It is anticipated that 10 young people will be recruited to the study. Participants will be excluded if they: (1) are not fluent in English, as participants will be asked to communicate their experiences of the running program with other participants; (2) are pregnant women; (3) have significant medical conditions for which they receive regular medical care, as this program will require participants to exercise three times a week, mostly outdoors; (4) have not been medically cleared for participating in a running program by a general practitioner (GP); and, (5) are in the acute phase of a psychotic illness.

Participants will also comprise 10 young people from the general population, to ascertain the feasibility of the running program with the use of internet enabled mobile devices among a selected sample of healthy controls. Inclusion criteria will include expressing an interest in participating in the running program. Exclusion criteria included: (1) not being fluent in English; (2) pregnant women; and, (3) having significant medical conditions. Participants will be recruited through friends and acquaintances of the research team.

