### Procedure

Members of the research team will raise awareness of the running program among EPPIC case managers by attending clinical meetings and distributing study brochures. Case managers will then be invited to refer suitable clients who might be interested in participating in the running program to the research team. Potential participants will meet with a Research Assistant (RA) who will explain all aspects of the study protocol except for one: that there is funding available to those who do not own a suitable pair of running shoes. It was decided not to inform all participants about this at the outset to avoid enticing people into participating for the wrong reasons. However, if a participant indicates that they would like to take part but are unable to because they do not have suitable running shoes, the RA would offer the participant support to purchase a pair of running shoes. Providing a good pair of running shoes to participants was considered important as this would play a significant role in minimising injuries from running and removing barriers to participation.

If the young person expresses an interest in taking part, the RA will obtain written consent from participants and their parent/guardian, where appropriate. Participants will also be provided with written information that explains the study details and the contact details of the research team. Mental state and capacity to provide consent will be determined both by the participant's case manager/doctor who are independent of the study and also by clinically experienced members of the research team.

Participants will be recruited at approximately the same time to form a virtual, co-located cohort of participants. Having provided their consent, participants will be shown how to use the technological components of the study, will be shown how to jog correctly if this is needed, and how to complete stretches before and after exercise. Given that young people experiencing first episode psychosis often present with significant medical co-morbidities [4], they will be screened for physical health conditions prior to starting the program by a general practitioner (GP). This was conducted to ensure that the intervention does not pose an unnecessary risk to participants. The GP will examine their medical history, prescribed medications, and general health status, paying particular attention to respiratory problems, diabetes and cardiac problems.

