### Outcomes and assessments

The main outcomes of interest are whether or not the running program is found to be feasible among patients with first episode psychosis, and whether or not the program is found to be acceptable. The feasibility of the running program will be determined by assessing adherence to the structure of the running program, the frequency with which participants make use of the social networking technology, whether or not participants spend some time after each run communicating their experiences with other participants via twitter, and whether or not participants complete the running program. The acceptability of the running program will be determined by assessing what participants like/dislike about the features of the running program and the technological components, and the motivating factors for continuing with the running program as reported by participants in their 'blog' posts on twitter. Secondary outcomes of interest are whether or not participation in the running program leads to higher levels of self-reported fitness, and whether or not there is a relationship between the use of the social networking website and the up-take of the exercise intervention.

These outcomes will be assessed via the completed interviews at week 4 and also at week 9. The interviews at both time-points will include a series of questions designed to elicit whether or not participants like or dislike the running program and the use of the social networking technologies, whether any members of the group influenced their participation in the program, participants' motivations and barriers to engaging in the program, and any changes in their perceived health and well-being. Additional questions at week 9 will include whether the goals for participating in the program were met, if there were any other features that participants would have liked to be included in the program, and their thoughts and priorities about engaging in physical activity at the completion of the program.

Outcomes will also be assessed via the 'blogs' made to the social network website after each running session, the interactions between participants on the social network website, and also via the uploaded results from the Nike+ sensor.

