If the research program is found to be feasible and acceptable to patients with first episode psychosis, the research team will seek funding to investigate the health benefits of this running program in a larger sample. Given that young people are increasing their usage of internet enabled mobile devices, and that these devices present new opportunities for the delivery of health services, it is important to rigorously examine how mobile devices might be incorporated and correctly utilised as an adjunct form of mental health intervention. Changing health behaviour for the long term requires maintaining a patient's motivation and interest over a protracted period of time [30]. The effective use of social networking to support such a behaviour change represents a significant gap in the current state of the research literature, particularly in relation to changing the exercise habits of patients with first episode psychosis. There appears to be a specific need for novel psychosocial interventions in addition to the use of medications in this population [31]; this study provides an avenue of possible research that uses technological components to promote exercise among patients with first episode psychosis. Ultimately, it is envisaged that exercise therapy may become part of routine clinical care as part of an evidence-based best practice multidisciplinary approach to mental healthcare.

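### Interest in running is required at entry in order to secure completion, yet completion and adherence are read as feasibility in first-episode patients generally, and no feasibility outcome shows uptake

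*Protocol article*

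**What the plan says.** The Participants section sets two inclusion criteria for patients: being a current EPPIC client, and that they "express an interest in participating in a running program, to ensure that they will complete the program and are willing to volunteer their time". On numbers it says: "It is anticipated that 10 young people will be recruited to the study".

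The Procedure section places an earlier step before this: "Case managers will then be invited to refer suitable clients who might be interested in participating in the running program". A research assistant then meets the potential participants. A general practitioner must clear patients before they start, and clients in the acute phase of illness are excluded.

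Outcomes and assessments gives the main question as "whether or not the running program is found to be feasible among patients with first episode psychosis", together with acceptability. It continues: "The feasibility of the running program will be determined by assessing adherence to the structure of the running program". The other three components are how often the social network is used, whether participants post after their runs, and "whether or not participants complete the running program".

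The Discussion makes the bid for a larger study conditional on the same population: "If the research program is found to be feasible and acceptable to patients with first episode psychosis".

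**The concern.** One section gives the securing of completion as a purpose of an entry criterion. Another treats completion, and the closely related adherence, as evidence of feasibility. The group that starts has been filtered twice for motivation, once by case managers and once by the interest criterion, but the conclusion is worded for patients with a first episode of psychosis in general.

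At stake is what a good result would mean. High completion among people who already wanted to run says little about patients who did not. The Background presents social networking as a means of overcoming poor motivation to exercise, and the Discussion says that studies are needed on how to raise participation, so the less motivated patients matter to the article's own rationale. If few clients accept the offer, a pilot with excellent completion among starters would not reveal it.

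**Working it through.** The plan states no completion rate, feasibility threshold or share of clients interested, so there is no figure of its own to reproduce. The check sets the sections side by side and then illustrates the size.

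**Step 1. Entry rule against outcome.** The interest criterion (Participants) is there partly to secure completion. Completion and adherence are two of the four feasibility components (Outcomes and assessments). There is no run-in and no screening on observed running, so completion can still vary among those who enter. Selection is on a presumed predictor.

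**Step 2. Population sampled against population named.** Sampled: EPPIC clients who are referred, interested, medically cleared and not acutely ill. Named in Outcomes and assessments and in the Discussion: first-episode patients, unqualified. The second is wider than the first.

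**Step 3. Does any listed outcome show uptake?** Adherence, frequency of network use, posting after runs and completion can be observed only in people who have entered. The secondary outcome that mentions uptake of the exercise relates it to use of the networking site and is assessed from participants' own interviews, posts and sensor data. It cannot count those who declined.

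**Step 4. Can the second group correct for this?** The 10 general-population participants are also admitted on expressed interest and come from the research team's friends and acquaintances. They do not represent uninterested patients.

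**Step 5. Illustration, all rates assumed.** Let s be the share of eligible clients who are interested, c1 completion among them and c0 completion among the rest. Completion among all eligible clients is s × c1 + (1 − s) × c0. With c1 = 0.80:

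| s | c0 = 0 | c0 = 0.40 |
|---|---|---|
| 0.20 | 0.20 × 0.80 = 0.16 | 0.16 + 0.80 × 0.40 = 0.48 |
| 0.50 | 0.50 × 0.80 = 0.40 | 0.40 + 0.50 × 0.40 = 0.60 |
| 0.80 | 0.80 × 0.80 = 0.64 | 0.64 + 0.20 × 0.40 = 0.72 |

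The result equals 0.80 only if c0 = c1 or everyone is interested.

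**Step 6. What 10 patients would show.** If 8 of 10 completed (assumed), the exact (Clopper-Pearson) 95% interval is 0.444 to 0.975. That is sampling error for interested clients only and says nothing about selection. The same 8 completers would be 8/20 = 40%, 8/50 = 16% or 8/100 = 8% of clients offered the program, for assumed numbers offered of 20, 50 or 100. These ratios count people who never started as not completing. They show how different the uptake behind one completion figure can be; they do not estimate how far the interest rule raises completion.

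**The case against.** The strongest reply is that this is ordinary volunteering. Every consenting study of a voluntary program enrols willing people. The interest criterion carries no motivation score or trial period, and a larger study would presumably also enrol volunteers, so interested clients are a relevant pilot group. The study is qualitative and exploratory and plans no population estimate. Completion is one of four components, and acceptability is a separate main outcome.

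Much of this stands. A reader might infer that the study selects on its own end point and that its completion result is therefore empty. The documents do not support that: nobody is admitted or refused because of completion, and the result remains informative for the group studied. Nor can medical clearance and the medical exclusions be read as selection on the outcome. Their stated reasons are the demands of the exercise and the avoidance of risk; they narrow the population and do no more. A reader might also infer that the next study formally depends on uptake. The Discussion makes it depend on feasibility and acceptability and does not mention uptake.

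A further reply is that recruitment counts belong to a full protocol or to the results paper. That would answer a complaint about missing detail. It does not answer this one, because the article itself states how feasibility will be determined and names the population for the conclusion. As written, those two statements do not match the group that is enrolled.

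**Conclusion.** The concern holds in a limited form. The plan admits patients on expressed interest with the declared aim of securing completion, then uses completion and adherence as part of feasibility for first-episode patients without qualification, and carries that population into the decision on a larger study. The findings will apply to interested clients and are likely to look favourable. They cannot support a general statement, and no listed component shows uptake.

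The direction rests on one assumption, that interest predicts completion, which the criterion's own stated reason shares. The size is unknown. The percentages in the working are illustrations, because the documents give neither completion nor uptake figures. The point is worth acting on, but it does not invalidate the pilot: the interviews and the adherence data keep their value for the group studied.

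**What to change.** 1. In Outcomes and assessments, add uptake to the feasibility components: the numbers of clients referred, approached, declining (with reason), not cleared by the GP, consented and started.
2. Report completion among starters alongside those counts.
3. In Outcomes and assessments and in the Discussion, state the conclusion for interested, referred, medically cleared, non-acute EPPIC clients.
4. Remove the completion rationale from the interest criterion. This corrects the wording only and changes nobody's eligibility.

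The cost is a short log and a narrower, slightly less favourable claim. The research assistant already meets the potential participants who are referred and can record everything from referral onwards. Clients who turn the program down with their case manager never reach the research assistant, so counting them needs a simple tally from case managers; without it, the report should say that the counts begin at referral. Recruitment, intervention and sample size stay as they are.

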### Materials

The running program will be delivered via an application implemented on an internet enabled mobile device, an iPod touch. The iPod touch is a product of Apple Inc, which incorporates a portable media player, a mobile Wi-Fi platform and a multi-touch graphical user interface. Two freely available applications will be downloaded onto the iPod touch for participants, the Couch to 5 k (C25K) application and the Nike+ iPod application. The C25K application will be utilised for guiding participants through the running program via audio cues, and will allow participants to listen to a playlist of songs of their choosing while completing their exercise. The Nike+ iPod application will be utilised to measure running activities from the Nike+ running sensor that will be attached to the participant's running shoe. The Nike+ sensor is similar to a pedometer that counts each step a person takes and calculates the distance travelled, duration of each run (time) and pace. Thus, the sensor can also act as a measure of program adherence by noting whether participants complete the scheduled exercises. Participants will also be provided with a sports armband to secure the iPod touch to their arm during the exercise, computer cables and earphones.

Participants will also be provided with a number of de-identified usernames and passwords with which they will be able to access the social networking website (i.e., Twitter), their email account, and Nike+ account. De-identified names will be used to ensure participants feel comfortable when writing about their running experiences and to protect their privacy. These will be set up specifically for the purpose of this research.

